### Randomization and blinding

The randomization at the level of the individual will be performed by a statistician at the Chinese Evidence-based Medicine Center, West China Hospital, Sichuan University. SAS procedure PROC PLAN will be used to generate the randomization schedule. An independent offsite investigator who is not involved in the enrollment or assessment of participants will be responsible for keeping the randomization schedule in sealed envelopes. After the baseline assessment, the independent offsite investigator will open an opaque envelope sequentially and assign each eligible participant to the corresponding group.

Due to the special designation of the therapeutic footwear, it is not possible to blind participants to their allocated group. Thus, this trial will be an open-label clinical study and blinding will not be adopted. For reducing bias, participants will not be informed which footwear is intended to provide improved outcome. Moreover, every effort will be made to ensure that the primary outcome assessors and the statistician remain blinded to treatment allocation until the end of the study.

### Study procedures

All participants will be invited to attend the baseline visit and five further study appointments for 12 months on post-randomization. Data at every visit will be collected in case report forms (CRFs) by the trial team. All data will be entered into a secure database by research assistants (i.e., data collectors). In the current trial and further ancillary studies, there are no plans for collection, laboratory evaluation, and storage of biological specimens for genetic or molecular analysis.

#### Baseline visit

After signing an informed consent, participants will be interviewed using a standard questionnaire to obtain information on demographic characteristics (including sex, date of birth, race, education, occupation, annual income, residence, family history and diabetic duration), lifestyle risk factors (physical activity, smoking status and alcohol consumption), history of past and present illness, and current medications. Blood pressure, height, weight and waist circumference will be measured with the use of standard methods. Fasting blood samples and urine sample will be collected to test blood routine, liver and renal function, eGFR, glucose, lipid, serum creatase, glycated hemoglobin (HbA1c), urine routine, and urinary albumin to creatinine ratio. Ankle brachial index (ABI) will also be measured using a pulse waveform analyzer BP-203RPE II (form PWV/ABI, Omron Healthcare Co., Kyoto, Japan).

Based on the above-mentioned information, eligible participants will be defined by an on-site investigator and then randomized to the study group or control group by an independent offsite investigator. Subsequently, every randomized participant will continue to perform plantar pressure tests by the trained podiatrist. Footscan® Pressure Measurement System (RSscan international NV, Paal, Blegium) will be used to obtain the data of plantar pressure. Before plantar pressures are measured, each participant will undertake at least two practice walks along the plate walkway to familiarize them with the experimental process. Then, each participant will be asked to walk in bare feet upon the footscan platform at self-selected gait speed for at least three successful trials. The foot data including peak plantar pressure will be recorded by the Footscan® pressure measure system, which automatically divided the foot into 10 masked regions: hallux, toes 2–5, first to fifth metatarsals, midfoot, medial heel, and lateral heel. Locations of previous ulceration, foot deformity or preulcerative signs will be the primary sites of interest. In additional, blood flow parameters of lower extremities, which include maximum systolic velocity, maximum diastolic velocity, and time-averaged mean velocity, will also be assessed by a vascular ultrasound specialist in the vascular ultrasound room of our hospital that is a quiet temperature-controlled environment. Measures will be performed at the same time of day for individual subjects.

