#### Secondary outcome measures

The secondary outcome measures include (1) the change of barefoot dynamic plantar pressures, from the third to the sixth diaries compared with that from the first diary (screening period); (2) the influence of footwear adherence on ulcer recurrence; and (3) the incidence of cardiovascular events.

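### Baseline plantar pressure is placed after randomisation in one section and before it in another, which exposes a secondary change endpoint to avoidable bias

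*Protocol article*

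**What the plan says.** Three sections of the protocol article bear on when the baseline plantar pressure is taken.

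- **Baseline visit.** After questionnaire, anthropometry, laboratory tests and ankle brachial index, "eligible participants will be defined by an on-site investigator and then randomized to the study group or control group by an independent offsite investigator". The next sentence reads: "Subsequently, every randomized participant will continue to perform plantar pressure tests by the trained podiatrist". Leg blood flow comes later in the same paragraph and "will also be assessed by a vascular ultrasound specialist in the vascular ultrasound room of our hospital"; its timing relative to randomisation is not stated.
- **Randomization and blinding.** "After the baseline assessment, the independent offsite investigator will open an opaque envelope sequentially".
- **Secondary outcome measures.** The plantar pressure endpoint is a change "compared with that from the first diary (screening period".

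On blinding, the Randomization and blinding section says that "it is not possible to blind participants to their allocated group", that "participants will not be informed which footwear is intended to provide improved outcome", and that efforts will be made so that "the primary outcome assessors and the statistician remain blinded to treatment allocation until the end of the study". Data management and the Discussion speak of blinded outcome assessment without limiting it to the primary outcome. Ethics and dissemination has a podiatric nurse or podiatrist deliver the footwear.

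In Statistical analysis, plantar pressure at baseline and at 3, 6, 9 and 12 months enters a repeated measures ANOVA. Blood flow is analysed as change at 12 months, by t test or by ANCOVA depending on whether the baseline means look comparable.

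**The concern.** A baseline should be fixed before anyone can know the allocation. Barefoot plantar pressure is the first listed secondary outcome and serves the second objective of the trial, and every later value is judged against this baseline. If the test follows allocation, knowledge of the arm could affect how a participant walks, which walks are accepted as successful, or how the sites of interest are identified. A difference between arms that arises in this way would enter the change analysis and could not be separated from an effect of the footwear. For blood flow, a baseline taken after allocation could also influence which test is used, because that choice depends on the baseline means.

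A second, smaller risk is missing data. Someone who withdraws between allocation and the test has been randomised but has no baseline pressure. Testing before allocation removes that gap.

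**Working it through.** **Order of steps, section by section**

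| Section | Baseline plantar pressure | Baseline blood flow |
|---|---|---|
| Baseline visit | After randomisation, explicitly | After it by sentence order only |
| Randomization and blinding | Before the envelope, if part of the baseline assessment | Same |
| Secondary outcome measures | Screening period, so before randomisation on a plain reading | Not listed as a secondary outcome |

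The wording under Baseline visit allows no other order for plantar pressure: the test comes next, and it is done on people already randomised.

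**Who is kept blind.** The explicit commitment names the primary outcome assessors and the statistician. The general statements in Data management and the Discussion may or may not cover the podiatrist who runs the pressure test and the ultrasound specialist. No section says whether either knows the allocation, or whether the podiatrist who tests is the one who delivers footwear. Their blinding is therefore not secured, which is different from shown to be absent.

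**Illustrative size.** The documents give no figure for an allocation-related shift, so its size b is an assumption. The scale comes from the pilot in the Discussion (99 patients, 177.07 ± 15.71 before and 172.67 ± 15.53 kPa after).

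- Difference: 177.07 − 172.67 = 4.40 kPa.
- SD: √((15.53² + 15.71²)/2) = 15.62 kPa, so 4.40/15.62 = 0.28 SD.
- The pilot p value reproduces as an unpaired comparison: SE = √((15.53² + 15.71²)/99) = 2.22, t = 4.40/2.22 = 1.98, p = 0.0489 (stated 0.049).
- A shift of 1 kPa is 1/4.40 = 23% of the pilot difference.

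Take 160 per arm, no true effect, two-sided 5% (sidedness is not stated), a shift b in one arm's baseline that is absent at follow-up, and a baseline to follow-up correlation ρ of 0.5 or 0.8 (assumed).

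- Change score: bias b, SE = 15.62 × √(2(1 − ρ)) × √(2/160), which is 1.746 (ρ = 0.5) or 1.105 (ρ = 0.8).
- ANCOVA: bias ρb, SE = 15.62 × √(1 − ρ²) × √(2/160), which is 1.512 or 1.048.
- False-positive rate = Φ(−1.96 + bias/SE) + Φ(−1.96 − bias/SE).

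| b (kPa) | Change, ρ 0.5 | Change, ρ 0.8 | ANCOVA, ρ 0.5 | ANCOVA, ρ 0.8 |
|---|---|---|---|---|
| 1 | 8.8% | 14.8% | 6.3% | 11.9% |
| 2 | 20.9% | 44.1% | 10.1% | 33.3% |
| 4.4 | 71.2% | 97.8% | 30.7% | 91.9% |

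With 128 per arm (the planned 20% dropout), b = 1 gives 8.1% and 12.8% for the change score, and 6.0% and 10.5% for ANCOVA. The change score stands in for the planned repeated measures ANOVA, in which baseline is one of the repeated values. The ANCOVA columns show that baseline adjustment reduces the problem but does not remove it.

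**If the shift persists.** If the same arm carries a shift b′ at follow-up, the bias in the change is b′ − b, which is zero when b′ = b. The table therefore applies only to a shift that is present at baseline and gone later.

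**The case against.** The strongest reply has five parts.

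1. *The contradiction may be verbal.* The baseline assessment that precedes the envelope could mean only the eligibility work-up, and the screening-period label could simply mean visit 1. This is possible, and the schedule in Fig. 3, which is not reproduced in the text at hand, might show the intended order. On that reading, however, the sections agree on taking the pressure baseline after allocation, so the weakness remains.
2. *Nothing says the testers are unblinded or that participants already know their arm.* This stands. A reader might infer both from the open-label design and from podiatrists delivering footwear. But allocation is made by an offsite investigator, no section says when participants learn their group, and they are not told which footwear is expected to do better.
3. *The measurement is hard to influence.* It is barefoot, follows practice walks, and the foot regions are divided automatically. The sites of interest (previous ulceration, deformity, preulcerative signs) exist before allocation, and no section has the new footwear worn first. This limits the risk. Self-selected speed, the acceptance of walks and some judgement about sites leave part of it.
4. *A lasting awareness effect would cancel in the change.* This is correct, and it limits the calculation above.
5. *Withdrawal between allocation and testing is speculative.* No section suggests that it is common, and Statistical analysis ties intention to treat to the primary endpoint, which needs no pressure baseline. The Abstract states the principle more generally. The point is minor.

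**Conclusion.** The point holds as a conflict over sequence with a consequence for secondary analyses. For plantar pressure, Baseline visit places the test after randomisation, against Randomization and blinding and the screening-period label in Secondary outcome measures. For blood flow the same order is suggested only by where the sentence stands.

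The consequence is exposure to avoidable bias in the change analyses, plus a small risk of missing baselines. It would go too far to say that the baselines are contaminated or that unblinded staff take them: the documents show no shift and do not settle the testers' blinding.

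The size is unknown. The increase from 5% to about 9% or 15% for a change-score comparison rests on an assumed 1 kPa shift in one arm that does not persist, on assumed correlations, and on an SD from an uncontrolled before-after pilot. It shows only that small shifts matter when the expected effect is itself about 0.28 SD. Time to ulcer recurrence, the primary endpoint, is not affected. The change should be made, but the main result of the trial does not depend on it.

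**What to change.** Amend Baseline visit so that plantar pressure, the sites of interest and leg blood flow are recorded after eligibility is confirmed and before the envelope is opened, with randomisation as the last step of the visit. In Randomization and blinding, say that the baseline assessment includes these measurements. In Secondary outcome measures, replace the diary and screening-period wording with the baseline visit before randomisation. Also state whether the podiatrist who tests and the ultrasound specialist are kept unaware of allocation at follow-up, because the new order protects only the baseline.

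The cost is the reordering of one visit. Nobody ineligible need be tested, because testing still follows confirmation of eligibility. Trial status gives recruitment as still to begin, so on that timetable the change could be made before the first participant. If anyone is tested under the current order, the time of the test relative to allocation should be recorded.

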### Participants

Patients with a history of DFU whose healing time of foot ulcer was over 3 months will be invited to participate in our trial by phone. Individuals will be eligible for the trial if they meet the following inclusion criteria: (1) aged ≥ 18 years, (2) type 1 diabetes (T1DM) or type 2 diabetes (T2DM), (3) decrease or loss of protective foot sensation due to/as a result of diabetic peripheral neuropathy, and (4) had a healed foot ulceration in the 3 months prior to randomization. However, individuals will not be enrolled into this trial if they meet the following exclusion criteria: (1) amputation proximal to the tarsometatarsal joint, (2) the use of walking aids that offload the foot, (3) severe lower extremity artery disease (ankle brachial index ≤ 0.4, intermittent claudication or rest pain), (4) osteoarticular diseases unrelated to T1DM or T2DM, (5) decrease or loss of vision that is difficult to treat or correct, (6) unstable cardiovascular disease or unstable ischemic cerebrovascular disease, (7) severe renal dysfunction (estimated glomerular filtration rate (eGFR) < 30 mL/min per 1.73 m^2^) or severe liver dysfunction (Child-Pugh grade C), (8) malignant tumor, (9) severe illness that would make 24-month survival unlikely (as judged by the patients physician), (10) pregnancy or breast-feeding women, (11) neurologic or psychiatric disease that may prevent compliance with the protocol, and (12) patients who are considered unsuitable for the trial by investigators.

Potential participants will be given a brief verbal explanation of the trial by their treating podiatrist. Research assistants will give them telephone interviews and invite patients who are willing to participate to our diabetic foot center for further confirming eligibility and baseline measurements. Written informed consent will be obtained by a trained and experienced podiatric nurse or podiatrist at the baseline visit. On the consent form, participants will be asked whether they agree to use of their data and biological specimens when they choose to withdraw from the trial and asked for permission for the research team to share their relevant data with people from the universities taking part in the research or from the regulatory authorities.

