### Sample size calculation

PASS 11.0 software was used to obtain sample size. As a parallel-group randomized controlled trial, the Log-rank Test (Lakatos) was used for the sample size calculation based on the following parameters or assumptions:
The survival probability of treatment group was estimated for 77.9%. According to the latest national multicenter survey data in China, 31.6% patients with a history of DFU developed new ulcer during 1 year follow-up [5]. Thus, the survival probability of control group was assumed to be 64.8%. We assume that the treatment group could have a 30% higher survival probability than control group.The accrual period for patients’ recruitment was estimated for 12 months. The accrual pattern would be equal. The follow-up period would be 12 months. Therefore, the total time of this trial would last 24 months.The power was set at > 0.8, while *α* was 0.05. The dropout rate of 0.2 was assumed. No switching between two groups. Two groups would have same sample size.

Therefore, the total sample size calculated using PASS was at least 314 cases. In this trial, we would recruit a total of 320 patients (160 for each group).

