#### Follow-up visits

Participants will be followed at 1 month (visit 2), 3 months (visit 3), 6 months (visit 4), 9 months (visit 5), and 12 months (visit 6) after randomization. At each visit, the trial team will collect the information including incidence of foot ulcer, footwear adherence, cardiovascular events, glucose profile, and other cardiovascular risk factors control. For physical activity evaluation, participants will be asked to wear a pedometer (P084, SPORTWAY, ShenZhen, China) every day to record the date and steps taken per day. Meanwhile, a concealed activity monitor (Lifecorder Plus, Suzuken) will be attached to the diabetic therapeutic footwear. Activity data will be uploaded by a research assistant to a centralized server via internet at each follow-up visit. Adherence to treatment will be evaluated through the comparison of the step counts recorded by a concealed activity monitor with those recorded by a pedometer. Adherence to treatment will be monitored until the end of follow-up. Plantar pressure distribution patterns will be measured after randomization every 3 months. At the end of follow-up, ABI and blood flow parameters of lower extremities will also be collected. At each visit, if participants make a withdrawal request or are not eligible to continue due to the presence of severe concomitant diseases or conditions listed in the exclusion criteria, they will be discontinued from the study. For participants who drop out, the information including incidence of foot ulcer, footwear adherence, cardiovascular events, ABI (if possible), plantar pressures (if possible), and biochemical parameters (if possible) will be collected.

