### Statistical analysis

At the end of this trial, all original data without participants’ name and the random sequences will be sent to a statistician for data analysis. Statistical analysis will be performed using SAS version 9.4 (SAS Institute Inc., Cary, NC, USA). Significance level will be set at *α* = 0.05. Quantitative variables expressed as means ± standard deviation or median with interquartile range, and categorical data will be recorded as numbers and percentages. Between-group differences of continuous variables will be tested for significance using Student *t* test when original data or data via transformation of variables is normally distributed or using Wilcoxon rank-sum test when data is not normally distributed. A chi-square test will be used for categorical data.

The primary end point, ulcer recurrence, will be analyzed according to the intention-to-treat principle, with event curves for the time to the first event on the basis of Kaplan–Meier analysis, and treatments will be compared by means of the log-rank test. A cox regression model will be used to calculate the hazard ratio for the primary end point. Among secondary end points, plantar pressures at baseline and at 3, 6, 9, and 12 months will be compared with repeated measures ANOVA. The changes blood flow parameters of lower extremity at baseline and at 12 months will be compared using Student *t* test when these means between groups are comparable at baseline or using analysis of covariance (ANCOVA) when these means are not equivalent at baseline. For cardiovascular events, the hazard ratio for the comparison of treatment group with control group and 95% confidence intervals will be estimated with the use of a proportional-hazards model.

The footwear adherence will be calculated for each group and then ulcer recurrence rates will be compared between the subgroups of patients with high adherence and low adherence by *χ*^2^ tests. We also plan to explore whether potentially important covariates such as age, sex, body mass index, physical activity, and diabetic duration could potentially confound the results.

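### Barefoot plantar pressure is scheduled and analysed by repeated measures ANOVA with no provision for participants whose ulcer recurs, so skipped tests would delete them unequally by arm

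*Protocol article*

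**What the plan says.** The test method appears only under Baseline visit. After randomization, "Subsequently, every randomized participant will continue to perform plantar pressure tests by the trained podiatrist", and "each participant will be asked to walk in bare feet upon the footscan platform at self-selected gait speed for at least three successful trials". At that point the ulcer has healed, because eligibility requires that the patient "had a healed foot ulceration in the 3 months prior to randomization". The regions that matter most are also fixed there: "Locations of previous ulceration, foot deformity or preulcerative signs will be the primary sites of interest".

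For follow-up, the Follow-up visits section says only: "Plantar pressure distribution patterns will be measured after randomization every 3 months". Secondary outcome measures defines the outcome as "the change of barefoot dynamic plantar pressures, from the third to the sixth diaries compared with that from the first diary", so the follow-up readings are barefoot too. Statistical analysis fixes the method: "plantar pressures at baseline and at 3, 6, 9, and 12 months will be compared with repeated measures ANOVA".

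None of these sections mentions recurrence. Under Follow-up visits, participation ends on a withdrawal request, severe concomitant disease or a listed exclusion condition; re-ulceration is not named. The only allowance for a pressure test that cannot be done applies to participants who drop out.

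**The concern.** Ulcer recurrence is the primary event, it is expected to be common, and it is expected to differ between arms. The pressure outcome is meant to show whether the footwear reduces plantar load, and it is read on the feet in which that event occurs.

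There are two ways to handle a participant with an open ulcer at a scheduled visit, and the article chooses neither. If the test is done, a reading from an ulcerated foot enters the same comparison as readings from intact feet, more often in the arm with more ulcers. If the test is not done, a reading is missing because of the primary outcome. A conventional repeated measures ANOVA needs all five readings, so one missed test removes the participant entirely, including the readings taken before recurrence. The pressure comparison would then lean towards participants who stayed ulcer-free, and more so in the control arm.

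**Working it through.** **Inputs from Sample size calculation.** One-year ulcer-free probability is 0.779 for footwear and 0.648 for control, with 160 per arm. The source survey reports that "31.6% patients with a history of DFU developed new ulcer during 1 year follow-up", which gives 1 − 0.316 = 0.684, not 0.648, so both control values are carried. The footwear value follows from the survey rate and a 30% reduction: 1 − 0.7 × 0.316 = 0.779. As a check that 0.648 and 0.779 underlie the stated total of at least 314, a Lakatos log-rank calculation (two-sided 5%, 80% power, 20% yearly loss, 12 months' accrual plus 12 months' follow-up) gives 311.

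**Re-ulcerated at least once by month m**, before dropout: 160 × (1 − S^(m/12)).

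| Month | Footwear (0.779) | Control (0.684) | Control (0.648) |
|---|---|---|---|
| 3 | 10 | 14 | 16 |
| 6 | 19 | 28 | 31 |
| 9 | 27 | 40 | 44 |
| 12 | 35 | 51 | 56 |

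The month-12 total is 86 to 92 of 320. The arms differ by 0.316 − 0.221 = 9.5 points, or 0.352 − 0.221 = 13.1 points.

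**Ulcers open at a test.** Healing time is not in the article. Assume exponential healing with mean D = 1.5 to 4.5 months, first recurrences only, no dropout. With l = −ln(S)/12 and r = 1/D, the proportion open at month t is p(t) = l/(r − l) × (exp(−l t) − exp(−r t)).

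Summed over months 3, 6, 9 and 12 and multiplied by 160, footwear has 16.9 tests on an open ulcer at D = 1.5 and 40.5 at D = 4.5. Control has 24.1 to 58.2 (0.684) or 26.8 to 65.0 (0.648). The total is about 41 to 106 of 320 × 4 = 1,280 scheduled tests, or 3% to 8%.

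**If those tests are skipped.** A participant is deleted if the ulcer is still open at the first test after onset. Over the four intervals that probability is p(3) × [1 + S^(3/12) + S^(6/12) + S^(9/12)].

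| Arm | p(3), D = 1.5 / 4.5 | Bracket | Deleted of 160 |
|---|---|---|---|
| Footwear | 2.59% / 4.40% | 3.651 | 15 / 26 |
| Control, 0.684 | 3.86% / 6.58% | 3.489 | 22 / 37 |
| Control, 0.648 | 4.37% / 7.46% | 3.424 | 24 / 41 |

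So roughly 37 to 67 of 320 would leave the ANOVA because they re-ulcerated, with more leaving from control in every case.

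**If those tests are done.** At month 12, p(12) is 2.5% to 7.3% for footwear, 3.4% to 10.2% for control at 0.684, and 3.7% to 11.2% at 0.648. At matching D the arms differ by 0.9 to 3.9 points. With an assumed shift of 10 to 30 kPa while an ulcer is open, the arm difference moves by 0.009 × 10 ≈ 0.1 kPa to 0.039 × 30 ≈ 1.2 kPa. The pilot change reported in the Discussion is 177.07 − 172.67 = 4.40 kPa.

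**The case against.** The strongest reply is that the detailed procedure belongs to the baseline visit, when ulcers have healed, and that a rule for the test day is the kind of detail a condensed article leaves to the full protocol. That stands as far as safety goes. A reader might infer that participants with open ulcers are made to walk barefoot on the plate, perhaps five times per visit. The article does not say so. It is silent about open ulcers at follow-up, a podiatrist runs the baseline test, and the practice walks are not said to be barefoot or repeated later. Some re-ulcerated participants may also leave the schedule, since using an offloading walking aid is an exclusion condition and so ends participation.

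A second reply is that pooling all readings is not an error. Recurrence follows randomization, so comparing every reading by assigned arm estimates the total effect of assignment. That also stands. Restricting the outcome to readings before recurrence would itself select on something the footwear is meant to change, so it should not be the main analysis.

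A third is that a shift of 1 to 4 kPa might be read from these rates. That needs the whole assumed shift in everyone who has ever re-ulcerated (9.5 to 13.1 points × 10 to 30 kPa). All participants already have a healed ulcer at entry, so the documents give no reason to apply it beyond open ulcers.

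The named analysis is what these replies do not answer. The article commits to repeated measures ANOVA, and in its conventional form that method cannot keep participants with a missed test.

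**Conclusion.** The point holds as a weakness in the named analysis and a gap in the follow-up schedule, not as a demonstrated safety exposure or a demonstrated bias of known size. That 86 to 92 of 320 re-ulcerate, unequally by arm, rests only on the plan's own rates before dropout. The deletion of about 37 to 67 participants also assumes that every test falling on an open ulcer is skipped, that healing takes 1.5 to 4.5 months on average, and that ANOVA is meant in its complete-data form. The 0.1 to 1.2 kPa distortion if tests are done adds the assumed 10 to 30 kPa shift. It could be negligible or up to about a quarter of the pilot change (1.2 / 4.4 = 0.27), and the article cannot settle which. The primary analysis is unaffected.

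**What to change.** In Statistical analysis, replace the repeated measures ANOVA with a mixed model for repeated measures on the 3, 6, 9 and 12 month readings, with arm, visit, arm by visit and baseline pressure, using all available readings by assigned arm. Add a sensitivity analysis limited to readings before first recurrence.

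In Follow-up visits, reconcile the 3-monthly barefoot test with the expected recurrences by stating whether the research test is done while an ulcer is open. Which rule applies is for the sponsor and investigators to decide. On the CRF, record ulcer status at each pressure visit and the reason for any test not done.

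The cost is one sentence in the schedule, two CRF items and slightly more analysis work. The mixed model assumes that readings not taken are missing at random given arm, baseline and earlier readings. The sensitivity analysis selects on recurrence and should be read with that in mind.
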